**Figure 2 fig2:**
[figure not shown]
Locations of scalp acupuncture lines and acupoints. Mannequin images were sourced from the 3D body application (v8.8.32).

### Acupuncture operation

2.12

During the operation, participants will be instructed to wear eye masks and perform the head stitch while seated. First, the location of the scalp acupoint will be identified, and the tip of the needle will be inserted diagonally below the subcutaneous fascia along the acupoint area from top to bottom. The needle should be positioned at an angle of 15° to 30° relative to the scalp, with the tip from the top down into the subcutaneous fascia and then advanced 0.5 to1.0 cun along the scalp acupoint line.

Participants will be then be instructed to perform body acupuncture procedures in a supine position. Once their breathing is stable and their bodies are fully relaxed, the following steps will be performed: The needle will be inserted straight into the acupoints LI4, SP6, and LR3. For LI4 and SP6, the insertion depth should range from 0.5 to 0.8 cun, whereas for LR3, the depth should range from 0.3 to 0.5 cun. The needles should be inserted at an angle of 15° to 30° from the skin surface to ensure proper stimulation.

Additionally, a straight insertion will be performed into LI11, CV12, ST25, and CV6. The insertion depth for LI11 and CV12 should be between 1.0 and 2.5 cun, while for ST25 and CV6, it should be between 0.8 and 1.0 cun. The needles should be inserted perpendicularly to the skin at a 90° angle.

Finally, the needle will be inserted from the outer side of the calf toward GB34 and ST36 at a 90° angle, either straight or obliquely, to a depth of 1.5 cun. The insertion should be done carefully to avoid discomfort. After insertion, the needles at LI11, CV12, ST25, CV6, ST36, and GB34 can be lifted and twisted gently to enhance stimulation, generating a local swelling sensation that indicates the achievement of deqi. In Traditional Chinese Medicine (TCM), deqi is a key concept in acupuncture and moxibustion, signifying the achievement of an optimal therapeutic state during the course of treatment (MacPherson and Asghar, 2006; Zhou et al., 2011).

During the procedure, sterile disposable filament needles, measuring between 25 and 40 mm in length and 0.25 mm in diameter will be utilized, along with appropriate fixation tools (details are presented in Figure 3). The needles are manufactured by Suzhou Huatuo Medical Equipment Company in China to ensure quality and safety.

**Figure 3 fig3:**
[figure not shown]
Device for acupuncture treatment and fixation. The device on the left is for the sham acupuncture group and on the right for the acupuncture group. Sham needles (blunt-tip design, left) were affixed with elastic fixation devices to mimic tactile stimulation without skin penetration.

All operators will undergo standardized training to adhere to the specified needle insertion angle, depth, and stimulation intensity. This training will encompass practical demonstrations and assessments to ensure consistent practice among practitioners, supplemented by regular skill evaluations and practice audits to maintain high standards of care.

### Sham acupuncture operation

2.13

The acupoints utilized in the sham acupuncture group will mirror those of the acupuncture treatment group. The sham acupuncture group will utilize non-penetrating retractable blunt needles and fixation tools that do not penetrate, which also measure between 25 and 25 mm in length and 0.25 mm in diameter, sourced from the same manufacturer (details are presented in Figure 3). Patients in this group will wear the same eye masks as those in the acupuncture group. The sham procedure will employ the same number of needles and last the same duration as the acupuncture procedure. Acupuncture points on the head will be secured with tape, while those on the body will be stabilized using the device depicted in Figure 3. All operational details will be meticulously documented.

### Baseline evaluation

2.14

During the baseline evaluation, the patient’s age, sex, disease duration, Hoehn–Yahr stage, UPDRS III scores, MMSE scores, MoCA scores, and levodopa equivalent dose (LED) will be assessed and recorded. To ensure the effectiveness of the study, assessments will be conducted at the same time each time the patient is in the on or off phase.

### Outcome assessment

2.15

Throughout the observation period, each patient will record detailed information regarding their medication use, including dose modifications and interactions with acupuncture. All PD patients will begin the tests 12 h after discountinuing their anti-PD medication (the off period) and will take their medication immediately after completing the test.

#### Primary outcomes

2.15.1

The UPDRS III assesses a patient’s motor function by measuring various aspects, such as language, facial expressions, tremors, rigidity, limb movements, posture, and gait. A lower UPDRS III score indicates a better quality of life (Movement Disorder Society Task Force on Rating Scales for Parkinson’s Disease, 2003). This evaluation will be performed prior to inclusion, 4 weeks post- treatment, and after 8 weeks of follow-up.

#### Secondary outcomes

2.15.2

##### The Berg balance scale

2.15.2.1

The Berg Balance Scale (BBS) is a widely utilized assessment tool that evaluates a patient’s capacity to maintain both dynamic and static balance through a series of functional activities (Park, 2018). Higher scores on this scale signify enhanced balance capability. This evaluation will be conducted prior to inclusion, after 4 weeks after treatment, and after 8 weeks of follow-up.

##### Gait test

2.15.2.2

Wearable gait analysis systems employ sensors and computer systems for gait quantification. By combining motion sensors worn on both feet, the systems can capture the three-dimensional (3D) attitude angle and motion trajectory. Abnormal parameters associated with gait posture can be identified by measuring gait frequency and amplitude stability. Subsequently, the data from the sensors are analyzed to provide a comprehensive gait assessment (Demonceau et al., 2015; Nancy Jane et al., 2016). An inertial measurement unit (IMU) developed by the School of Mechanical Engineering at Zhejiang University will be utilized to analyze the gait of patients with PD (Wang et al., 2019). After the patient traverses a distance of 20–40 m on level ground, an IMU will be positioned 3–5 cm above the ankle, to record data at a frequency of 100 Hz. The data stored on the SD card will include the gait cycle, gait speed, gait frequency, maximum moving speed, proportion of swing period, and proportion of support period. This evaluation was conducted prior to inclusion, after 4 weeks after treatment, and again after 8 weeks of follow-up.

##### Resting-state fMRI

2.15.2.3

Resting-state fMRI measures blood-oxygen-level-dependent (BOLD) signals without the requirement of specific tasks, providing insights into spontaneous brain activity. All patients will undergo scanning prior to inclusion and 4 weeks post-treatment. A Siemens MAGNETOM Skyra 3.0 T scanner will be utilized to acquire MRI images. To minimize head movement during data collection, all patients will be fitted with foam pads. Additionally, to mitigate scanning noise, patients will be instructed to close their eyes and refrain from thinking of anything other than falling asleep. Two functional images (rest1 and rest2) and 3D T1-weighted images will be acquired from the scan. The fMRI parameters will include 32 axial slices, a repetition time (TR) of 2,000 ms, a echo time (TE) of 30 ms, a slice thickness of 3.5 mm, a flip angle (FA) of 90°, a matrix size of 64 × 64, and a field of view (FOV) of 224 × 224 mm^2^. The scan parameters for the T1-weighted structural image will be as follows: 256 slices, TR = 2,530 ms, TE = 2.98 ms, thickness = 1.0 mm, FA = 7°, matrix = 256 × 256, and FOV = 256 × 256 mm^2^.

Data will be analyzed using RESTplus (v1.2) software (Jia et al., 2019). The data will be preprocessed through the following steps: (1) 10 time points will be removed at the begininning of the scan to ensure the stability in the patient’s condition and allow for adaptation. (2) Correction of slice timing for different slices within an image. (3) Rearranging scans over time. (4) Resampling to the Montreal Neurological Institute space with a voxel size of 3 × 3 × 3 mm^3^. (5) Spatial smoothing using a 6 mm full width at half maximum Gaussian kernel to reduce individual mismatches. (6) Linear trend removal. (7) White matter signals, Friston-24 head motion parameters, and cerebrospinal fluid signals will be included in covariate regression. (8) Low-pass filtering will be applied between the range of 0.01 to 0.08 during the regression (Dunn et al., 2011).

Several calculation indicators, including Regional Homogeneity (ReHo), the amplitude of low-frequency fluctuations (ALFF), and functional connectivity (FC), have been proposed to assess brain activity and are considered more reliable (Zang et al., 2004; Zou et al., 2008; Arbabshirani et al., 2013). ALFF reflects the level of spontaneous activity in each brain region, with abnormal alterations in ALFF values indicating atypical neural activity. Conversely, abnormal increases in ReHo values suggest enhanced consistency in local spontaneous activity. Additionally, FC aims to establish connections between different brain regions based on temporal correlations.

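### As written, the resting-state fMRI instruction directs patients toward sleep; the sentence, possibly a wording slip, should be corrected before ALFF, ReHo and FC are interpreted

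*Protocol article*

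**What the plan says.** Section 2.15.2.3 describes resting-state fMRI as recording the BOLD signal "without the requirement of specific tasks, providing insights into spontaneous brain activity". A few sentences later it gives the patient instruction. It opens with the reason, "Additionally, to mitigate scanning noise", and continues that "patients will be instructed to close their eyes and refrain from thinking of anything other than falling asleep". Each session yields two functional runs, labelled rest1 and rest2, plus a structural image; how the two runs are to be used is not stated. Table 1 places the scans at baseline and week 4.

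The indices are "Regional Homogeneity (ReHo), the amplitude of low-frequency fluctuations (ALFF), and functional connectivity (FC"). On the nuisance terms the section says: "White matter signals, Friston-24 head motion parameters, and cerebrospinal fluid signals will be included in covariate regression". The Abstract lists fMRI among the secondary outcomes. Section 2.16.3 carries ALFF, ReHo and FC into correlations with microbiota and serum metabolites, and into a mediation analysis of a microbiota–metabolite–brain pathway.

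**The concern.** The sentence is an operating instruction for a secondary outcome. Taken at its word, it leaves patients lying with their eyes closed and one thing to think about: falling asleep. That sits badly with the stated aim of a task-free scan, because trying to fall asleep is itself a directed mental state. The stated reason does not fit either, since an instruction about thoughts does not reduce scanner noise.

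If some patients sleep and others do not, or the same patient sleeps at one visit only, the three indices may reflect vigilance as well as whatever else changed. The section reads the indices as brain function: "ALFF reflects the level of spontaneous activity in each brain region, with abnormal alterations in ALFF values indicating atypical neural activity". A shift caused by sleep would look the same. The values are then used again in the multimodal analysis, so the problem would carry forward. That vigilance can move these indices is an assumption here; the article does not discuss it.

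**Working it through.** The article gives no figure on this point, so there is none to reproduce. The check has two parts.

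**1. The text, side by side**

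- Purpose of the scan (2.15.2.3): spontaneous activity, no task.
- Instruction (same section): eyes closed, falling asleep as the only permitted thought.
- Reason given (same section): scanner noise.
- Regressors (same section): white matter, cerebrospinal fluid and 24 head-motion parameters. None stands for sleep.
- Elsewhere in the article: no sentence tells patients to stay awake, so nothing overrides the literal reading.

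The instruction and the purpose do not agree, and the instruction and its reason do not agree.

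**2. What sleep could do, on assumed values**

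Assumptions, none of them from the article: sleep shifts an index by *s* = 0.25 to 1.0 SD, and a share *p* of patients is asleep. The number per arm, 29, and the illustrative effect, 1.15/1.54 = 0.747 SD, are borrowed from Sample size estimation (2.9). They were set for UPDRS III, not fMRI, and serve only as a scale. Power and false-positive rates use the normal approximation for one index, two-sided 0.05.

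*Equal sleep in both arms.*
- Between-arm bias = *s*(*p* − *p*) = 0.
- Variance = 1 + *s*²*p*(1 − *p*).
- Smallest case, *s* = 0.25, *p* = 0.3: 1 + 0.0625 × 0.21 = 1.013.
- Largest case, *s* = 1.0, *p* = 0.5: 1 + 1 × 0.25 = 1.25.
- Power for 0.747 SD is about 0.81 without sleep. It is 0.807 in the smallest case and 0.72 in the largest.
- Noise of this kind, unrelated to the other variable, shrinks a correlation by about 1/√variance: 1/√1.013 = 0.99 to 1/√1.25 = 0.89. For the Spearman coefficients planned in 2.16.3 this is only approximate.

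*Sleep differs between arms by 10 or 20 percentage points.*
- Difference due to sleep = *s* × difference in share: 0.25 × 0.10 = 0.025 SD to 1.0 × 0.20 = 0.20 SD.
- Chance of a significant result with no direct brain effect, using SE = √(variance × 2/29): 0.051 at the low end. At the high end (50% versus 30% asleep, *s* = 1.0, variance 1.23), SE = 0.291 and the chance is 0.106.

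*Sleep differs between visits.* The same product applies to change within one arm: a 10- to 20-point change in the share asleep moves mean change by 0.025 to 0.20 SD. If both arms change alike, this cancels in the comparison between them.

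*Mediation.* Randomisation protects the comparison of arms. It does not protect the metabolite-to-brain association, which could be distorted if sleepiness in the scanner is also related to metabolites or microbiota.

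**The case against.** The strongest reply is that this is a language slip. Changing one or two words would give an ordinary resting-state instruction, and the article has other slips: a sham needle length range with the same value at both ends (2.13), a filter called low-pass but given a lower and an upper limit (2.15.2.3), and a gait sensor apparently fitted after the walk (2.15.2.2). This stands as a likely explanation. It does not remove the need for correction, because anyone working from the printed text would follow the literal wording.

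The second reply concerns bias. A reader might infer that the fMRI indices are bound to mix sleep with the acupuncture effect, or that the randomised comparison is biased. The documents do not support that. Both arms get the same instruction, allocation is randomised 1:1, the comparator is sham and patients are blinded (2.8). Equal sleep adds noise only, and greater familiarity at the second scan applies to both arms. If needling itself altered sleepiness, the resulting difference would be a real consequence of treatment. It would be hard to interpret, but it would not be a false difference. This reply stands in full for the comparison of arms.

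Third, a reader might count the lack of a wakefulness check or of ear protection as a defect. An article may leave such scanning detail to the full protocol, so neither is held against the plan.

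Fourth, the article's account of ReHo and ALFF describes what the indices measure and attributes nothing to acupuncture. That is fair; the concern lies in how changes would later be read.

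**Conclusion.** The point holds as a wording fault in an operating instruction. The literal text steers patients toward sleep in a scan meant to capture task-free activity, gives a reason that does not fit, and is not corrected anywhere in the article. Whether patients were or will be told this is unknown.

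If the text is followed, the consequences are extra noise in ALFF, ReHo and FC, possible distortion of within-arm change and of the correlation and mediation analyses, and difficulty interpreting a between-arm difference if acupuncture affects sleepiness. The size cannot be known from the documents. The ranges shown rest wholly on assumed sleep rates and shifts, and they include zero bias between arms, the neutral case under one common instruction.

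The primary outcome, UPDRS III, and the sample size are untouched. The affected measures are a secondary outcome and mechanistic work that the article itself calls preliminary. The correction is worth making because it is nearly free and because sleep status not recorded at the scan cannot reliably be recovered later.

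**What to change.** Replace the sentence with: eyes closed, stay awake, think of nothing in particular. If a different instruction is in use, state that one. Remove scanner noise as the reason. This costs one sentence.

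At small further cost, ask one wakefulness question after each of the two runs and report the answers by arm and visit. This needs no extra scan or staff.

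Keep all scans in the main analysis. Use awake-only runs solely as a sensitivity analysis, with the rule fixed in advance, applied blind to arm, and covering patients for whom both runs or neither qualifies. Restricting the main analysis to awake runs would select on a state that arises after randomisation. If acupuncture changes sleepiness, that selection could itself bias the comparison, and choosing blind to arm would not prevent it.

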#### Multimodal data analysis

2.16.3

In this study, we will conduct a comprehensive multimodal data analysis by integrating fMRI metrics including ALFF, ReHo and FC, with gut microbiota alpha and beta diversity, as well as differential serum metabolite levels. To explore the associations among these variables, we will utilize Spearman correlation analysis, which is well-suited for assessing non-parametric relationships. The Bonferroni correction will be applied to adjust for multiple comparisons. Additionally, mediation analysis will be performed to validate the hypothesized “microbiota-metabolite-brain function” pathway, examining how gut microbiota may influence brain function via specific metabolites. This integrated approach aims to provide deeper insights into the complex interactions among these biological systems.

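### As listed, the fMRI pipeline smooths the data before ReHo is calculated, which inflates and compresses an index of similarity between neighbouring voxels

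*Protocol article*

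**What the plan says.** Section 2.15.2.3 (Resting-state fMRI) opens the processing description with "The data will be preprocessed through the following steps" and gives a single numbered list of eight steps. Step 4 is "Resampling to the Montreal Neurological Institute space with a voxel size of 3 × 3 × 3 mm^3". Step 5 is "5) Spatial smoothing using a 6 mm full width at half maximum Gaussian kernel to reduce individual mismatches". Detrending, covariate regression and temporal filtering follow as steps 6 to 8.

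The next paragraph of the section introduces ReHo, ALFF and FC together. No separate branch is given for any of them. It interprets ReHo as follows: "abnormal increases in ReHo values suggest enhanced consistency in local spontaneous activity".

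Section 2.16.3 (Multimodal data analysis) uses the index again, "by integrating fMRI metrics including ALFF, ReHo and FC, with gut microbiota alpha and beta diversity".

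No sentence says outright that ReHo is computed from the smoothed series, and none says that it is computed from unsmoothed data. The order follows from the one common list.

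**The concern.** ReHo is a rank concordance between a voxel's time course and those of its immediate neighbours. A Gaussian kernel twice as wide (at half maximum) as the voxel replaces each series by a weighted average over those same neighbours. Part of the similarity that ReHo then reports was put there by the preprocessing.

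The other two indices are not affected in this way. ALFF is an amplitude, and FC as described here links different regions, so smoothing does not manufacture the quantity that they measure.

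At stake are the interpretation of ReHo as local consistency of activity, within a named secondary outcome, and the Spearman correlations of section 2.16.3. The mediation analysis in that section refers only to brain function and does not name ReHo, so its exposure is possible but not fixed by the text.

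**Working it through.** The plan states no figure for this point, so there is none to reproduce. The check asks what the stated kernel does to ReHo on the stated grid.

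**Inputs from section 2.15.2.3.** Kernel 6 mm FWHM; voxels 3 mm; "a repetition time (TR) of 2,000 ms"; and "Low-pass filtering will be applied between the range of 0.01 to 0.08 during the regression" (no unit given; taken as a 0.01–0.08 Hz band).

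**Assumptions not in the document.** ReHo as Kendall's W over 27 voxels; 230 retained volumes (170 also tried); spatially white noise; interpolation at step 4 ignored; and the signal models below.

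**Step 1: kernel width.** σ = 6 / 2.3548 = 2.55 mm, which is 2.55 / 3 = 0.85 voxel.

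**Step 2: correlation induced between face neighbours.** For independent noise, r = exp(−d² / 4σ²) = exp(−9 / (4 × 2.548²)) = 0.71.

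**Step 3: ReHo of pure noise.**
- Unsmoothed, the expected value is 1/27 = 0.037. Simulation gives 0.036 to 0.038.
- Smoothed, the mean pairwise correlation over the 3 × 3 × 3 block (self-pairs included) factorises by axis. Each axis has 3 pairs at offset 0, 4 at offset 1 and 2 at offset 2, with correlations 1, 0.7071 and 0.7071⁴ = 0.25. This gives [(3 + 4 × 0.7071 + 2 × 0.25) / 9]³ = 0.703³ = 0.35.
- Simulation of the rank-based index gives 0.321 (170 volumes) and 0.335 (230 volumes). Rank correlations run slightly below the product-moment values in the formula.

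Pure-noise ReHo therefore rises roughly ninefold, from about 0.04 to about 0.33.

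**Step 4: range of the index when 20% and then 60% of voxel variance is truly shared.**

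| Signal model | Unsmoothed | Range | Smoothed | Range |
|---|---|---|---|---|
| One signal common to all voxels | 0.24 to 0.60 | 0.36 | 0.92 to 0.98 | 0.06 |
| Localised field, σ 1 voxel | 0.11 to 0.27 | 0.16 | 0.52 to 0.58 | 0.06 |
| Localised field, σ 2 voxels | 0.18 to 0.47 | 0.29 | 0.72 to 0.79 | 0.07 |

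Single runs of the common-signal model vary a little. With 170 volumes the unsmoothed range was 0.548 − 0.215 = 0.333 and the smoothed range 0.979 − 0.905 = 0.074. With 230 volumes they were 0.553 − 0.203 = 0.350 and 0.979 − 0.901 = 0.078.

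**Step 5: does smoothed ReHo still respond to real homogeneity?** Yes. In the common-signal model it goes from about 0.33 (no shared variance) to 0.90 (20%) to 0.98 (60%), and it also rises in both localised models.

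**The case against.** **The order is inferred.** The article is condensed, and a branch specific to one index could sit in a fuller document. This lowers certainty about what the team will do. It does not remove the point, because the article states kernel, voxel size and sequence in a numbered list without exception. That is a stated order, not a detail left out.

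**A reader might infer that ReHo would measure the kernel instead of the brain.** The calculations do not support this. Smoothed ReHo still rises with true homogeneity under every model tried; it is distorted, not replaced.

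**A reader might infer that a group difference in ReHo would be an artefact.** The same list applies to both randomised arms and both scans, so the kernel does not by itself produce a false difference between groups.

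**A reader might infer a ceiling effect, or a fixed loss of power.** Both depend on the simulation model. Values near 0.9 and above arise when one signal is shared by every voxel. With localised signals and shared variance of 20% versus 30%, smoothed ReHo was 0.52 versus 0.54, or 0.73 versus 0.76, which is no ceiling. Nor is raw compression the same as lost power, because the spread also shrinks. For that 20% versus 30% contrast, the standardised difference fell from 3.15 to 2.56 under the common signal (0.59 / 3.15 = 19%), but from 9.3 to 1.9 and from 5.3 to 1.9 under the localised signals. Some loss of sensitivity appears each time, but its size cannot be fixed from the document.

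**The unsmoothed baseline of 0.04 is too low for real data.** The acquired in-plane voxel is 224 / 64 = 3.5 mm, resampled to 3 mm. Linear interpolation (type assumed) of white noise gave an unsmoothed ReHo of about 0.14. This stands: the rise from 0.04 to 0.33 describes smoothing in an idealised case.

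**Reach is limited.** ReHo is one of three indices in one secondary outcome, plus an exploratory analysis, and the raw scans allow correction later. This also stands.

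**Conclusion.** The point holds in a limited form. Followed as written, the list has ReHo calculated on series already smoothed at 6 mm on a 3 mm grid. Under the stated assumptions this lifts pure-noise ReHo from about 0.04 to about 0.33. It also narrows the raw range between 20% and 60% shared variance from about 0.16–0.36 to about 0.06–0.07. The direction was the same under all three signal models; the exact figures depend on the model, the neighbourhood and the omitted interpolation.

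The consequence is an inflated, compressed and less specific index. That weakens the local-consistency interpretation in section 2.15.2.3 and the use of ReHo in section 2.16.3. It does not invalidate the randomised comparison of ReHo, and it leaves the primary UPDRS III analysis and the sample size untouched. It should be corrected before the scans are analysed.

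**What to change.** In section 2.15.2.3, add a sentence stating that for ReHo step 5 is omitted, the remaining steps are run on unsmoothed data, and the resulting ReHo map is smoothed at 6 mm FWHM before group statistics. Keep step 5 in its present place for ALFF and FC. Section 2.16.3 should draw its ReHo values from these maps.

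The cost is one sentence and one additional software run on existing scans, with no burden on patients or scanner time. If the team already processes ReHo this way, the sentence simply corrects the published description.
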